## 5 STUDY DESIGN

### Study endpoints

The primary and secondary endpoints of this study are shown in table 1

Table 1: study endpoints

| Primary endpoint                          | Descriptions                                                                                                                                                             |
|-------------------------------------------|--------------------------------------------------------------------------------------------------------------------------------------------------------------------------|
| 1. Knowledge of intranasal corticosteroid | The mean scores of participants who correctly answer each question in the control and intervention groups with regard to the intranasal corticosteroid.                  |
| 2. Symptom control                        | The mean difference in symptom control between the control and interventional groups.                                                                                    |
| 3. Medication adherence                   | The mean adherence rate difference for the number of doses of intranasal corticosteroid spray taken by the participant between the control and interventional groups.    |
| 4. Quality of Life                        | The mean difference in quality of life between the control and interventional groups.                                                                                    |
| Secondary endpoint                        | Within group changes from Day 0, to Day 60 $\pm$ 7, Day 120 $\pm$ 7 and Day 180 $\pm$ 7 for knowledge level, symptom control, medication adherence, and quality of life. |

### Study design

This study will be conducted at the Hospital Raja Permaisuri Bainun in the state of Perak, Malaysia. A pharmacist-led educational protocol that has been validated by the researchers in other study will be adapted as an interventional tool for this study. This pharmacist led-protocol consists of patient education material and structured pharmacist counselling.

This trial is a single-centre, randomised, two-arm, and parallel-group controlled trial that will be conducted to determine the effectiveness of the pharmacist-led educational protocol. Adult patients diagnosed with moderate to severe AR who attend an outpatient ENT (ear, nose and throat) clinic in Hospital Raja Permaisuri Bainun will be recruited and randomly allocated at a 1:1 ratio into control and intervention groups.

The control arm will receive the current standard of pharmaceutical care, i.e., it is a health service that patient obtaining their medication from the outpatient pharmacy following a session of medical consultation at the ENT clinic, whereas the intervention arm receives the educational material and pharmacist counselling plus standard pharmaceutical care.

Baseline data will be collected and both groups will be followed up post-randomization on Day  $60 \pm 7$ , Day  $120 \pm 7$  and Day  $180 \pm 7$ . Participants will be contacted virtually (Zoom, Google Meet, or Whatapps call, or telephone call) or face-to-face, depending on the feasibility and standard operating procedures of the outpatient ENT (ear, nose, and throat) clinic at Hospital Raja Permaisuri Bainun during the follow-up on Day  $60 \pm 7$  and Day  $120 \pm 7$ . Meanwhile, the end-of-study follow up will be done at the routine scheduled clinic visit, which is around Day  $180 \pm 7$ .

### **Diagram of study design**

The study design of a prospective, randomized, controlled, parallel group trial is shown in Diagram 1.

Diagram 1: Design of a prospective, randomized, controlled, parallel group trial

## Study population

Patients who attended ENT outpatient clinic at Hospital Raja Permaisuri Bainun in the period of study that fulfil the study criteria as below:

### Inclusion

1. Malaysian, aged 18 to 80, with medical diagnoses of moderate to severe allergic rhinitis graded according to ARIA guidelines, who attended an ENT outpatient clinic in the period of study, and
2. capable of reading and writing in English or Malay

### Exclusion Criteria:

1. Pregnant or lactating mothers.
2. Patients who had comorbid diagnosis of chronic rhinosinusitis.
3. Patients who had psychiatric problems or dementia, at the discretion of the physician, were deemed unfit to participate in this study.
4. Patients with terminal illnesses, at the discretion of the physician, are unfit to participate in this study.
5. Patients with comorbidities or diseases, at the discretion of the physician, are unfit to participate in this study.
6. Patients with post-covid conditions with symptoms that continue beyond 3 months after being infected, at the discretion of the physician, are unfit to participate in this study (UpToDate, 2022).

## Sample size

Prior data indicate that in determining patients' knowledge level with regard to the use of intranasal steroids for AR treatment, the mean score of adults with adequate knowledge about allergic rhinitis treatment among controls is estimated to be 1.39 (SD:0.71), and the estimated true mean score of adequate knowledge for interventional subjects is 1.70 (SD: 0.58) assuming 77 participants in each group (Retinasekharan et al., 2021). By using the G-power calculator, this study will need 67 interventional participants and 67 control participants to be able to reject the null hypothesis that the mean scores of the interventional

and control groups are equal with probability (power) 0.8. The Type I error probability associated with this test of this null hypothesis is 0.05. The calculation is shown below:-

Sample size estimation for the mean difference of knowledge level between groups

Intervention group

Mean score: 1.70

Standard Deviation: 0.58

Control group

Mean score: 1.39

Standard Deviation: 0.71

Pooled standard deviation

$$\begin{aligned} \text{Pooled } SD &= \sqrt{\frac{(n_1 - 1) \times SD_1^2 + (n_2 - 1) \times SD_2^2}{n_1 + n_2 - 2}} \\ &= \sqrt{[(77-1) \times 0.71^2 + (77-1) \times 0.58^2] / (77+77-2)} \\ &= 0.648267 \end{aligned}$$

Results of the G-power calculator:

F tests - ANOVA: Repeated measures, between factors

Analysis: A priori: Compute required sample size

|                                     |             |
|-------------------------------------|-------------|
| Input: Effect size f                | = 0.2005347 |
| α err prob                          | = 0.05      |
| Power (1-β err prob)                | = 0.80      |
| Number of groups                    | = 2         |
| Number of measurements              | = 3         |
| Correlation among repeated measures | = 0.5       |
| Output: Noncentrality parameter λ   | = 8.0830473 |
| Critical F                          | = 3.9128750 |
| Numerator df                        | = 1.0000000 |
| Denominator df                      | = 132       |
| Total sample size                   | = 134       |
| Actual power                        | = 0.8057571 |

To determine the sample size required for the mean difference of symptom control between the intervention and control group, studies using TNSS as a symptom control evaluation tool, with the study design of a randomised controlled trial, recruiting a study population of intermitent or persistent AR, and possibly in Asian countries, were searched. The information from a randomised controlled trial that investigated the change in TNSS after an intervention vs. a placebo in adults in China with intermittent or persistent AR was used to estimate the sample size (Han et al., 2011). The G-power sample size calculator is used by setting the probability (power) at 0.8, the Type I error probability associated with this test of this null hypothesis at 0.05, the effect size at 0.3850550, and the function of repeated measures,

between factors ANOVA analysis. A sample of 18 participants is required for each group.  
The calculation is shown below.

Sample size estimation for the mean difference of symptom control between groups

Intervention group

Mean score: 3.991

Standard Deviation: 2.2145

n=181; reference: (Han et al., 2011)

Control group

Mean score: 5.704

Standard Deviation: 2.2341

n=182 reference: (Han et al., 2011)

Pooled Standard Deviation:

$= \sqrt{[(181-1) \times 2.2145^2 + (182-1) \times 2.2341^2] / (181+182-2)}$

$= 2.2243$

Results of the G-power calculator:

F tests - ANOVA: Repeated measures, between factors

Analysis: A priori: Compute required sample size

Input: Effect size f = 0.3850550

α err prob = 0.05

Power (1-β err prob) = 0.80

Number of groups = 2

Number of measurements = 4

Correlation among repeated measures = 0.5

Output: Noncentrality parameter λ = 8.5401995

Critical F = 4.1300177

Numerator df = 1.0000000

Denominator df = 34.0000000

Total sample size = 36

Actual power = 0.8102902

Therefore, 18 samples are required for each group

The mean of adherence rate to intranasal corticosteroid among control is 76.62 (SD: 2.848386), while the adherence rate for the intervention group is 93.94 (SD: 2.84) (Feng et al., 2017). By using G-power calculator, we will need to study 2 intervention and control groups, respectively, to be able to reject the null hypothesis that the adherence for intervention and control participants is equal with a probability (power) of 0.8. The Type I error probability associated with the test of this null hypothesis is 0.05. The calculation is shown below:-

525 Intervention group  
 526 Mean: 93.94  
 527 Standard Deviation: 2.84  
 528 n=16; reference: (Feng et al., 2017)  
 529  
 530 Control group  
 531 Mean score: 76.62  
 532 Standard Deviation: 2.848386  
 533 n=13; reference: (Feng et al., 2017)  
 534  
 535 Pooled Standard Deviation:

$$536 \quad Pooled\ SD = \sqrt{\frac{(n_1 - 1) \times SD_1^2 + (n_2 - 1) \times SD_2^2}{n_1 + n_2 - 2}}$$

537 Pooled standard deviation  
 538 =  $\sqrt{[(16-1) \times 2.84^2 + (13-1) \times 2.848386^2] / (16+13-2)}$   
 539 = 2.843730

541 Results of the G-power calculator:

542 **F tests - ANOVA:** Repeated measures, between factors

543 **Analysis:** A priori: Compute required sample size

544 **Input:** Effect size f = 3.0289576

545 α err prob = 0.05

546 Power (1-β err prob) = 0.80

547 Number of groups = 2

548 Number of measurements = 3

549 Corr among rep measures = 0.5

550 **Output:** Noncentrality parameter λ = 55.0475049

551 Critical F = 18.5128205

552 Numerator df = 1.0000000

553 Denominator df = 2.0000000

554 Total sample size = 4

555 Actual power = 0.9350969

556

557 A study mapping the naso-ocular symptom scores to EQ-5D-5L utility values was referred to  
 558 in order to obtain the input of mean scores and standard deviation to estimate the sample  
 559 size required to compare patients' QoL between two groups. The EQ-5D-5L utility values in  
 560 mean and standard deviation were corresponding to the disease severity in AR patients,  
 561 where the utility values of  $1.000 \pm 0.000$ ,  $0.943 \pm 0.085$ ,  $0.909 \pm 0.095$ ,  $0.849 \pm 0.142$ , and  
 562  $0.767 \pm 0.175$  were corresponding to none, mild, moderate, severe, and most severe groups  
 563 (Kumanomidou et al., 2022). In this study, patients with moderate to severe allergic rhinitis  
 564 will be recruited for control and interventional groups, and the aim of the intervention is to  
 565 improve the symptoms, if not totally absence of symptoms, at least the mild disease state.  
 566 Assuming that the control group patients would remain in the disease status of moderate to

severe and the intervention group would achieve mild disease status, the EQ-5D-5L utility values corresponding to moderate ( $0.909 \pm 0.095$ ) and mild ( $0.943 \pm 0.085$ ) were selected to simulate the mean utility score of control and intervention, respectively.

The G-Power sample size calculator is used, and by setting the function of a repeated-measure ANOVA statistical test, the probability (power) at 0.8, the Type I error probability associated with this test of this null hypothesis at 0.05, and the effect size at 0.1885976, the sample size of 70 is calculated for each group as shown in the formulation of the calculation below.

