## 3 OBJECTIVES

### Primary Objective

To determine the effectiveness of the pharmacist-led educational protocol in managing allergic rhinitis between a control group of patients who are receiving standard pharmaceutical care and an interventional group of patients receiving an educational interventional protocol plus standard pharmaceutical care, based on the following specific parameters: -

1. Knowledge of intranasal corticosteroids
2. Symptom control
3. Medication adherence
4. Quality of life

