## **Statistical analysis**

An intention-to-treat analysis will be used to include all of the patients who were assigned to each group after randomization. The data analysis will be done using SPSS version 20.0. Descriptive data will be expressed as mean and standard deviation (SD) if the data is normally distributed, or median and interquartile range (IQR) if the data is not normally distributed. Categorical data will be presented in frequency and percentage.

To determine the knowledge level, The “yes” answer will be given a score of two, the “no” answer will be given a zero score, and “not sure” will be given a score of one (Retinasekharan et al., 2021). The outcome will be presented in mean score and standard deviation for each group. Each question will be analysed separately. The knowledge levels will be assessed at baseline, Day 120 $\pm$ 7 and on Day 180  $\pm$ 7. Between-group comparisons will be analysed using Two-way repeated measure ANOVA to compare mean score different between two groups. Meanwhile, the two-way repeated measures ANOVA will show the findings for the within-group comparison. A P-value of < 0.05 will be considered statistically significant.

The Total Nasal Symptom Score (TNSS) is the sum of scores for each of nasal congestion, sneezing, nasal itching, and rhinorrhoea at each time point, using a four-point scale (0–3), where 0 indicates no symptoms, a score of 1 for mild symptoms that are easily tolerated, a

score of 2 for awareness of symptoms that are bothersome but tolerable, and a score of 3 is reserved for severe symptoms that are hard to tolerate and interfere with daily activity. A higher score indicates the more severe the symptoms are, and the main outcome of TNSS will be generated as a mean and standard deviation. A mean score will be calculated separately for the past 12 hours and past 2 week. A two-way repeated measure ANOVA analysis will be employed to determine the mean difference between the scores of the control group and the interventional group in order to determine the overall effectiveness of the intervention. Within-group comparisons will be shown as part of the outcome of the two-way repeated measures ANOVA. A value of  $P < 0.05$  is considered statistically.

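### Knowledge is sized as one comparison at 80% power but analysed as four separate question tests, so the 80% is not the power of any defined conclusion about knowledge

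*Combined protocol and SAP*

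**What the plan says.** - **Primary Objective** (section 3): "Knowledge of intranasal corticosteroids" is listed once, as one of four parameters.
- **Sample size** (section 5): the knowledge calculation is headed "Sample size estimation for the mean difference of knowledge level between groups". It uses a control mean of 1.39 (SD 0.71), an intervention mean of 1.70 (SD 0.58) and one null hypothesis: "The Type I error probability associated with this test of this null hypothesis is 0.05". The run is labelled "F tests - ANOVA: Repeated measures, between factors" and returns 134 participants, 67 per group. No question is named.
- **Study endpoints, Table 1**: the endpoint is given by question: "The mean scores of participants who correctly answer each question in the control and intervention groups".
- **Study variables, Table 2, and Appendix E**: there are four questions, each answered yes, not sure or no.
- **Statistical analysis**: answers score 2, 1 or 0, then "Each question will be analysed separately". The threshold is stated without adjustment: "A P-value of < 0.05 will be considered statistically significant".

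No section defines a total or mean over the four questions, names a main one, or says how many must be significant. The TNSS is treated differently: its four symptom items are summed into one score for each recall period.

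**The concern.** The objective asks one question about knowledge and the sample size section attaches one power to it. Followed exactly, the analysis returns four P values and no stated way to turn them into an answer. If the intervention truly improves knowledge, the report may show significance on some questions and not on others, and the plan does not say whether the primary parameter was then met. That choice would be made after the data are seen. A single three-level item is also a coarse measure, and testing items one at a time gives up the precision gained by combining them.

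**Working it through.** **1. Reproduce the plan's figure.** Between-factor repeated-measures ANOVA: λ = f² × N × m / (1 + (m − 1)ρ), noncentral F on 1 and N − 2 degrees of freedom. The Sample size section gives f = 0.2005347, m = 3, ρ = 0.5, N = 134.

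λ = 0.2005347² × 134 × 3 / 2 = 8.083; critical F = 3.913; power = 0.8058. This matches the printed output.

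**2. Effect size implied by the stated means.** Pooled SD = √((0.71² + 0.58²)/2) = 0.6483. f = (1.70 − 1.39)/(2 × 0.6483) = 0.2391. The f entered corresponds to a difference of 2 × 0.2005 × 0.6483 = 0.26, not 0.31. Both values are carried forward.

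**3. Power for one question at the planned 70 per group (N = 140).**
- f = 0.2005: λ = 8.445, power 0.823.
- f = 0.2391: λ = 12.005, power 0.931.

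**4. Four questions with the same true effect.** For independent tests at f = 0.2005, all four are significant with probability 0.8227⁴ = 0.458, none with (1 − 0.8227)⁴ = 0.001, and one to three with the remaining 0.541. For correlated tests, four normal statistics with mean √λ were simulated (400,000 draws). The documents give no correlation between questions; 0 to 0.5 is assumed.

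| f | Correlation | All four significant | One to three significant |
|---|---|---|---|
| 0.2005 | 0 | 46% | 54% |
| 0.2005 | 0.5 | 60% | 38% |
| 0.2391 | 0 | 75% | 25% |
| 0.2391 | 0.5 | 81% | 18% |

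**5. What do 1.39 and 1.70 describe?** Both fit the 0–2 range of one question. They could also be averages. A 0–2 score with mean μ has variance at most μ(2 − μ): 0.848 for 1.39 and 0.51 for 1.70. For a mean of four questions with equal means, the stated SDs need an average between-question correlation of at least (4 × 0.71²/0.848 − 1)/3 = 0.46 and (4 × 0.58²/0.51 − 1)/3 = 0.55. The documents do not settle which reading applies.

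**6. One averaged score, only if the means are single-question values.** Averaging three questions with common correlation r multiplies f by √(3/(1 + 2r)). If only k of the three improve, f is also multiplied by k/3. At f = 0.2005 and N = 140:

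| Questions improved | r = 0.3 | r = 0.5 | r = 0.7 |
|---|---|---|---|
| 3 of 3 | 0.98 | 0.94 | 0.90 |
| 2 of 3 | 0.75 | 0.65 | 0.58 |
| 1 of 3 | 0.26 | 0.22 | 0.19 |

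For a like-for-like comparison, three separate tests at f = 0.2005 split (one or two significant) in 44% of trials at correlation 0 and 31% at 0.5.

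**The case against.** The best defence is that Table 1, Table 2 and the Statistical analysis section agree with each other: the endpoint is defined by question and analysed by question. On that view knowledge is tested as defined, and 80% is the power for one such test. This stands as far as it goes. A reader might infer that the 80% belongs to a test that is never run, or that knowledge is never tested. The documents support neither. The sizing means fit a single 0–2 question, and every question is tested. What the defence does not supply is which question was sized, or how four results become one conclusion on a parameter that the objective lists once.

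A second objection is that the split rates depend on inputs. This also stands: they more than halve when f follows from the stated means, and they assume an equal effect on every question. The plan does not require all four to be significant, so the all-four percentages describe how results would scatter, not the power of a planned criterion.

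Third, an average is not always better. If only one of three questions improves, its own test has power 0.82, against 0.26 to 0.22 for the average at correlations 0.3 to 0.5.

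Fourth, the point overlaps with multiplicity. It does so only in part. A Bonferroni level of 0.05/4 = 0.0125 would still leave four answers, and at f = 0.2005 and N = 140 it would lower power per question to 0.65.

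**Conclusion.** The point holds as a gap between objective, sizing and analysis. The 80% is the power for one unnamed question or for an untested average, and in neither case for a defined conclusion about knowledge. Under a true, equal effect on four questions with 70 per group, mixed results occur in 54% to 38% of trials at the entered f and in 25% to 18% at the f implied by the stated means, for assumed test correlations of 0 to 0.5.

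These figures take the plan's model as given, including an effect present at all three measurements, baseline among them; whether that is reasonable is a separate matter. The averaged-score powers apply only if 1.39 and 1.70 are single-question values.

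A reader might also infer that the trial is too small. That does not follow from this point: EQ-5D-5L utility sets the size at 70 per group, above the 67 for knowledge. The harm is to interpretation of a primary parameter, so the change should be made but does not affect recruitment.

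**What to change.** 1. In Table 1 and the Statistical analysis section, define one primary knowledge score per participant: the mean of the three factual questions in Appendix E, each scored 0–2 for correctness. Fix the scoring key first. At present a yes earns 2 on every question, including the one on long-term side effects, and the fourth question is a self-rating.
2. Test that score once between groups. Report the separate questions as descriptive or supportive.
3. In the Sample size section, state whether 1.39 and 1.70 are single-question or averaged values, and restate the power for the score actually tested. If they are already averages, the three-question powers shown above must not be used, because the averaging would be counted twice.

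The cost is wording only: no new data and no extra participants. The downside is that question-level P values lose confirmatory standing and an uneven effect is diluted. At f = 0.2005 and correlations of 0.3 to 0.5, power falls to about 0.75 to 0.65 if two of three questions improve, and to 0.26 to 0.22 if only one does. If the investigators prefer to keep question-level tests, they would need to name a lead question, or to set a decision rule with multiplicity control in advance.

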#### Formula of Pooled Standard Deviation:

$$\text{Pooled SD} = \sqrt{\frac{(n_1 - 1) \times SD_1^2 + (n_2 - 1) \times SD_2^2}{n_1 + n_2 - 2}}$$

Pooled standard deviation

$$= \sqrt{[(238-1) \times 0.095^2 + (238-1) \times 0.085^2] / (238+238-2)}$$

$$= 0.090139$$

#### Sample size estimated using G-power calculator:

**F tests** - ANOVA: Repeated measures, between factors

**Analysis:** A priori: Compute required sample size

|                |                                   |             |
|----------------|-----------------------------------|-------------|
| Input:  | Effect size f                     | = 0.1885976 |
|                | $\alpha$ err prob                 | = 0.05      |
|                | Power (1- $\beta$ err prob)       | = 0.80      |
|                | Number of groups                  | = 2         |
|                | Number of measurements            | = 4         |
|                | Corr among rep measures           | = 0.5       |
| Output: | Noncentrality parameter $\lambda$ | = 7.9674683 |
|                | Critical F                        | = 3.9097293 |
|                | Numerator df                      | = 1.0000000 |
|                | Denominator df                    | = 138       |
|                | Total sample size                 | = 140       |
|                | Actual power                      | = 0.8003899 |

Therefore, a sample size of 70 are required for each group.

To estimate the sample size required to compare EQ-5D VAS between two groups, the input for the control group was derived from a study that evaluated general health-related quality of life among allergic rhinitis patients, where the mean and standard deviation score of EQ-5D VAS reported was  $72.1 \pm 19.0$  (Hoehle et al., 2017); whereas the input for the intervention group was derived from a study assessing QoL in the general Malaysian population with a reported mean and standard deviation of EQ-5D VAS at  $85.5 \pm 12.3$ , with

the rationale that the intervention group would achieve QoL similar to the general population (Shafie et al., 2019). By using the G power calculator and setting the function of a repeated-measures ANOVA statistical test, the probability (power), the Type I error probability associated with this test of the null hypothesis to 0.05, and the effect size to 0.3244754, the sample size of 25 is calculated for each group as shown in the formulation of the calculation below.

